**FIGURE 1 F1:**
[figure not shown]
Strategies developed by researchers by a database of free images (freepik.com) to evaluate what the users will be able to do as a result of playing serious game. **(A)** Strategy “Set up your bedroom.” **(B)** Strategy for mapping activities before bedtime. Figures adapted from freepik.com by researchers and respecting terms and conditions to use.

#### Strategy for Mapping Activities Before Bedtime

This strategy was also developed by researchers and assesses the activities that the child usually does at night and before sleep. Each child will receive one kit with one sheet of paper A3 and fifteen stickers that represent common activities that they could do before sleep at night, such as: take a bath, play video games, brush their teeth, watch TV, read, listen to music, do homework, turn off the lights (**Figure 1B**). After that, they will read and apply the following instruction: “I would like you to select the stickers that represent activities that you do at night and before sleep. Do not paste stickers of activities that you would like to do. If the stickers lack any activity you can draw it.” Similarly to the strategy described above, this one will be used to measure the knowledge the children have and what they are able to do as consequence of playing serious game (Calderón and Ruiz, 2015).

#### Pictorial Sleepiness Scale of Maldonado

Sleepiness levels will be assessed by an adapted version (Belisio, 2014) of the Pictorial Sleepiness Scale of Maldonado (Maldonado et al., 2004). It will be applied during six consecutive class days between 02:00 pm and 03:00 pm, following class schedule. The data collected in the first day will be excluded from the analysis to decrease effects of a new person in the classroom. In the application the children will be requested to indicate the face on the scale that best represented how they were feel at the time, that is, if they felt sleepy or not. Higher scores indicate elevated levels of somnolence.

#### Evaluation of Serious Game “Perfect Bedroom: Learn to Sleep Well” by Children

For the purpose of allowing the children to evaluate the serious game, we developed a questionnaire with textual and graphics elements. It includes quality characteristics that current literature indicate to be relevant to evaluate serious games (Calderón and Ruiz, 2015) and contains questions on:

(1) User’s satisfaction and user’s experience, to evaluate their attitude and behavior related to the game.(2) Understandability, to assess the ability of the serious game of being understood.(3) Enjoyment, to assess if the game provides a fun experience to the users.(4) Learning outcomes, to identify what the users will be able to do as a result of playing this serious game. These measures will be provided from comparisons between the results from pre and post-intervention of the strategies “Set up your bedroom” and “Mapping activities before bedtime.”

## Stepwise Procedures

### Participants

This study aims to recruit 176 healthy children enrolled in two private schools from Natal (Rio Grande do Norte – Brazil), as the number of children per class in these educational institutions ranges from 23 to 28. Schools will be selected by convenience, as there are difficulties to promote parental and school involvement (Jones et al., 2013; Wilson et al., 2014; Mindell et al., 2016), due to the concern of staff and parents about the activities developed in school and the necessity to adjust the research schedule to that of school activities, such as evaluation periods, vacation, science fair or school games. Furthermore, sample size was carried out using G^∗^Power 3.1.9, with alpha level of 5%, effect size of 0.5, and power of 95% for the two groups (Faul et al., 2007; Aberson, 2015). Results from this analysis indicated 88 participants to each group.

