### Proposed Analysis

The software IBM (Statistical Package for the Social Sciences [SPSS], 1968), version 21.0 will be employed for data analysis, assigning the 5% significance level for all statistical tests. The Kolmogorov–Smirnov (KS) Test will be used to verify normality. Inferential and descriptive statistics will be used to test hypothesis.

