### Intergroup and Intragroups Analysis

Once confirmed that the groups did not present significative differences, the comparison procedure will be conducted. Variables included in sleep patterns (sleep latency, sleep efficiency, sleep and waking up times, total sleep time), sleep hygiene and sleep problems will be considered dependent variables and will be compared between experimental and control groups, during the three points in time where they will be evaluated, using independent student’s *t*-test and chi-square (χ^2^) with odds ratio and dimension of association (Phi and Cramer’s V), depending on the nature of the data. It will allow us to identify if the intervention with the serious game yielded improvements in objective sleep measures and sleep hygiene.

To evaluate possible improvements intragroup, comparisons will be conducted using: ANOVA (F) for repeated measures with Bonferroni’s post test and Q Chochran test. For all numeric variables percentage will be calculated with delta differences (post-test score minus the pre-test score) and percentage’s change [(post-test score) minus (pre-test score) divided by (pre-test score) multiplied by 100]. These measures will allow us to evaluate the intervention’s immediate effects and the maintenance of this effect after 4 weeks.

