Presence of electronic media in the bedroom (e.g., television, video game, and computer) and the use of them next to bedtime are related to late bedtime and decreased sleep duration. In addition, children that sleep next small screens (e.g., smartphones) relate impacts in perception of insufficient rest, probably caused by waking up due to notifications on the small screen (Cain and Gradisar, 2010; Falbe et al., 2015). The opposite is also true, and children that do not have electronics in the bedroom report more hours of sleep. Other factors related to the bedroom are also relevant, such as providing a comfortable bedroom and conditions to sleep, but this is challenging for families of low SES (Chung et al., 2014; Bagley et al., 2015).

Our serious game includes recommendations in sleep environment, but just the game is not enough to help children in families with low-incomes. Provide conditions, such as quiet and dark bedroom and comfortable bed, depends on the neighborhood that the families live and their incomes. Thus, subsequent interventions should include actions to help these families provide a comfortable bedroom, such as Time’s Beds for Kids in EUA (Mindell et al., 2016).

It stands-out that in Brazil did not exist, in our knowledge, any questionnaire adapted and validated to evaluate the chronotype of children with ages between 7 and 8 years, as different types have influences on the presence of sleep disorders and accentuate inadequate sleep habits (Jafar et al., 2017), so chronotype influence was not assessed in this protocol.

Other pitfall that could be noted, is the consideration that parent’s reports may be influenced by social desirability, indicating good sleep hygiene practices instead of the real situation. Another important challenge is to promote parental involvement, since previous researches indicated a decrease in participation over the evaluation periods (Jones et al., 2013; Wilson et al., 2014; Mindell et al., 2016). In this way, we proposed follow-up meetings with parents to minimize this decrease on participation.

Although in this protocol efficacy measures in evaluation will be limited to sleep habits and patterns, the promotion of optimal sleep has consequences in multiples domains (e.g., cognitive, health, temperament) that are sometimes completely forgotten in sleep programs interventions (Blunden, 2017). Thus, future studies should include other outcomes to evaluate efficacy, such as cognitive and academic performance.

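### The stated 95% power with 88 per group matches only an undeclared one-sided test with every recruited child analysed; read as two-sided, it is about 91% before exclusions

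*Protocol article*

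**What the plan says.** All of the following is in the protocol article.

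- **Sample size (Participants).** The G*Power calculation was run "with alpha level of 5%, effect size of 0.5, and power of 95% for the two groups". The outcome is given as "Results from this analysis indicated 88 participants to each group". The kind of effect size, the test and the number of sides are not named.
- **Recruitment (Participants).** "This study aims to recruit 176 healthy children", which is 2 × 88.
- **Significance level (Proposed Analysis).** The plan is "assigning the 5% significance level for all statistical tests", with nothing on one or two sides.
- **Tests.** Intergroup and Intragroups Analysis compares the groups "using independent student’s *t*-test and chi-square", and uses repeated-measures ANOVA and Cochran's Q within groups. Controlling for Covariates uses the same t-test and chi-square test to check that the groups are alike at baseline.
- **Exclusions.** Materials and Equipment removes from the analysis children who are absent from the intervention. Design and Procedures drops individuals with missing data.
- **Expected losses (Anticipated Results).** "previous researches indicated a decrease in participation over the evaluation periods". Follow-up meetings with parents are planned to limit this. No loss rate is given anywhere.

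**The concern.** A power statement is useful only if its inputs describe the analysis that will be run. Here alpha, effect size, power and sample size agree under two conditions that the article does not establish: a one-sided test, and no loss from analysis of any recruited child.

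If the between-group t-test is run two-sided at 5%, the chance of missing a true effect of d = 0.5 is about 9% rather than 5%, and exclusions raise it further. A reader weighing a null result against the stated 95% would then credit the trial with more sensitivity than it has. Leaving sidedness open also leaves a choice that could be made after the data are seen. A one-sided 5% test chosen in the observed direction has twice the false-positive rate of a two-sided 5% test.

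**Working it through.** **Inputs from the Participants section:** alpha 5%, effect size 0.5, power 95%, 88 per group, 176 recruited.

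**Assumptions, because the article does not say:** the effect size is Cohen's d (difference divided by SD), the test is a two-sample t-test with 1:1 allocation, and the loss rates below are illustrative.

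**Formula.** With n per group, df = 2n − 2 and noncentrality λ = d·√(n/2). Let T follow a noncentral t distribution with these parameters.
- One-sided power = P(T > t₀.₉₅,df).
- Two-sided power = P(T > t₀.₉₇₅,df) + P(T < −t₀.₉₇₅,df).

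**1. Reproducing the plan's figure.** For n = 88: df = 174 and λ = 0.5·√44 = 3.317.
- One-sided: critical value 1.654, power 95.1%. Solving for 95% gives n = 87.3, so 88. This is an exact match.
- Two-sided: critical value 1.974, power 91.0%. Solving for 95% gives n = 104.9, so 105 per group (210 in total).

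Other common designs with effect size 0.5 do not give 88 per group:
- Mann-Whitney (normal efficiency): 93 per group one-sided, 110 two-sided
- paired t: 45 or 54 in total
- one-way ANOVA with f = 0.5: 54 in total
- chi-square with w = 0.5: 52 to 80 in total for 1 to 5 df
- repeated-measures ANOVA, between-groups effect, f = 0.5, three times, assumed correlation 0.5: 37 in total

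**2. Detectable effect.** Holding n = 88 and solving two-sided power = 95% for d gives d = 0.546, about 0.55.

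**3. Losses.** Analysed n = 88 × (1 − loss), rounded down, with equal losses in both groups assumed:

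| Assumed loss | Analysed per group | Two-sided power | One-sided power |
|---|---|---|---|
| 0% | 88 | 91.0% | 95.1% |
| 10% | 79 | 87.8% | 93.1% |
| 20% | 70 | 83.6% | 90.3% |
| 25% | 66 | 81.4% | 88.7% |

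Even one-sided, losing one child per group (n = 87) gives 94.95%, just under the stated figure.

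**4. Allowance needed if 95% two-sided were kept after losses.** 105/(1 − loss) gives 105/0.90 = 116.7, so 117 per group at 10%, and 105/0.80 = 131.3, so 132 per group at 20%.

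**The case against.** The strongest reply is that the number is not wrong. The stated inputs give exactly 88 for a one-sided t-test, and the hypotheses in the Introduction are directional: longer and more efficient sleep, shorter latency, less sleepiness. No section says the tests are two-sided, and a condensed article may leave sidedness to a fuller document. F and Cochran Q tests are planned only within groups, so their nature does not settle how the between-group t-test will be run.

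This stands in part. A reader might infer that the planned tests are two-sided and that the 95% is therefore an arithmetic error. The documents do not support that: sidedness is unstated, and the figure is right for one set of conditions. But a directional hypothesis does not by itself declare a one-sided test, and an unqualified 5% is ordinarily read as two-sided. The same t-test at the same level also serves the baseline comparison, which looks for differences in either direction.

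On losses, it is fair that the rates are assumed and that parent meetings may reduce them. Allocation is also described as involving children with valid data, which may mean some screening beforehand. The exclusion for absence would fall mainly on the experimental group, since controls receive the game only after all evaluations. Equal losses are thus a simplification: 20% lost from one group only (70 against 88, λ = 0.5·√(70·88/158)) leaves 87.3% two-sided and 92.8% one-sided. None of this supplies an allowance, because the recruitment target still equals the number to be analysed.

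A reader might also expect class-level randomisation to lower these figures further. That is a separate question and no part of this point rests on it.

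**Conclusion.** The point holds as a mismatch between the stated power and the analysis as written, at moderate severity. The figure of 88 with 95% power is correct for a one-sided 5% t-test with complete data, and the article establishes neither condition. On the conventional two-sided reading, the shortfall is about 4 percentage points before any exclusion. The gap from losses exists on either reading, but its size depends on rates that the documents do not give.

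The conclusion rests on taking 0.5 as Cohen's d in a two-sample t-test. That is the likely reading, because it returns 88 exactly. Power stays above 80% in every case tabulated, so the design is not undermined; what needs correcting is the claim made for it. A reader might also infer that a null result will be taken as evidence of no effect. No section proposes that, so it is a risk to guard against and not a fault in the plan.

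**What to change.** Before analysis, state that the between-group tests are two-sided at 5%, and name the effect size as Cohen's d for a two-sample t-test if that is what was used. Restate power as about 91% at d = 0.5 with 88 analysed per group, followed by the range under loss rates labelled as assumptions (for example 88%, 84% and 81% at 10%, 20% and 25%).

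If 95% is kept as the claim, either quote 105 analysed per group as its basis, or declare and justify the one-sided test. In both cases say that the figure holds only before exclusions.

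Restating costs a sentence or two and a less favourable power figure, with no extra enrolment. Delivering 95% two-sided would take 210 analysed children instead of 176, plus an allowance for losses.

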### Design and Procedures

It will be used an experimental, prospective, quantitative and randomized controlled trial to compare effects of game application on change of habits and parameters of sleep, besides what the users will be able to do by playing this serious game. In order to achieve that, the following steps will be conducted: (1) randomization of participants to allocate each one in experimental or control group; (2) use of a control group that should not be submitted to intervention, to infer highest internal validity; (3) intervention with experimental group, which will allow us to evaluate if there was any modification in the parameters evaluated, determining the validity of the intervention and (4) evaluation of participants at three distinct moments throughout the study, namely: pre-intervention, immediate post-intervention and follow-up assessment, after 4 weeks (Suresh, 2011).

After selecting the schools by convenience, experimental and control groups are selected by two processes of randomization. The first will select which classes will compose the experimental and control groups in each school, throughout a basic method of randomization that is flipping a coin; in other words, one situation will be associated with each side of coin (e.g., heads – control and tails – experimental) to determinate the assignment of each class. Second, the function “Randomly assign subjects to groups” in online software GraphPad^1^ will be used to allocate participants of each class with valid data for analysis to each group.

Upon enrolment, the four stages of research will be followed, counting on the participation of children and their parents/guardians. All encounters with parents/guardians will happen at 6:40 pm, after the children’s classes, due to the parent’s convenience. First, during the stage of pre-intervention, questionnaires and scales will be applied to assess sociodemographic data, and characterize sleep habits and sleep pattern, by filling out the UNESP sleep habits and hygiene scale (child version) and sleep diary, besides giving the actiwatch to be wore by the children. Parents will also answer the Sleep Disturbance Scale for Children to identify the presence of sleep disorders. After this, parents from experimental group will participate in a workshop conducted by the research team about sleep habits and the importance of healthy sleep in childhood. The team will be available for an additional encounter 1 week after evaluation to clarify doubts about filling in the sleep diary and/or use of actiwatch.

The children themselves will be active in the evaluation steps. All evaluations with them will occur on the first Monday after each meeting with parents, once research begins with the parent’s authorization. In this stage, the children will answer the Pictorial Sleepiness Scale of Maldonado to evaluate sleepiness levels and will characterize their bedroom and the activities that they do before sleep at night, using, respectively, the strategies “Set up your bedroom” and “Mapping activities before bedtime.”

After pre-intervention evaluation, the experimental group will be submitted to the intervention with our serious game “Perfect Bedroom: learn to sleep well,” which will be conducted by three researchers during the children’s classes, at 02:00 pm on Tuesdays and Thursdays (see section “Intervention”).

The control group will follow the institution’s school activities defined on the school schedule. The only moments of contact with study staff will be during evaluation, pre-, post and following intervention, to assure a proper control condition, in accordance to our research question about intervention works (Holmes et al., 2018). Considering this, further control will be needed for the following factors: contact with research team limited only to evaluation periods to avoid confusing factors such as attention, warmth, or human relationships. In the evaluation stages, the guardians will answer questionnaires and scales to assess sociodemographic and health data, sleep habits and sleep pattern of their child. The children themselves will answer: a scale to assess sleepiness levels, a questionnaire to evaluate the serious game and the game itself, will characterize their bedroom and the activities they perform before sleep. Also, teachers will be informed only essential information about the study and will be instructed to not use the knowledge acquired about sleep in class during the period of the research.

After completion of the intervention, the last two steps, post intervention evaluation and follow-up evaluation, will be conducted after 4 weeks. In these stages sleep habits and sleep patterns will be re-evaluated by the parents. Additional encounters 1 week after each evaluation will be provided to clarify any doubts about filling in the sleep diary and/or use of actiwatch. During these steps the children will be required to answer the Pictorial Sleepiness Scale of Maldonado and to characterize their bedroom and any activities that they perform before sleep at night (**Figure 2**). Thus, there will be three meetings with parents/guardians during evaluation steps, with three more other encounters to elucidate any doubt about assessments. Missing data will result in individuals being excluded without outcome.

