## Abstract

Promoting a healthy sleep is a big challenge and becomes a strategic priority in public health, due to the severe consequences on children’s development and risk to psychiatric diseases. Interventions that promote healthy sleep, such as those that focus on the dissemination of behavioral and environmental recommendations of sleep hygiene with children, are presented as an alternative. Serious game design offers wide-reaching domains in health applications and is increasing in popularity, particularly with children and teens because of it’s potential to engage and motivate players differently from other interventions. This study aims to evaluate effects of serious game on sleep hygiene recommendations “Perfect Bedroom: learn to sleep well,” on sleep habits and sleep parameters of healthy children. This is an experimental, prospective and quantitative study. We will randomize children in experimental (*n* = 88) and no intervention groups (*n* = 88). The experiment has four stages (pre-intervention, intervention, post-intervention, and follow-up), which will count with participation of children and their parents/guardians. In the evaluation stages, the guardians will answer questionnaires and scales to assess sociodemographic and health data, sleep habits and sleep pattern of their child. The children themselves will answer the following: a scale to assess sleepiness levels, a questionnaire to evaluate the serious game and the game itself, will characterize their bedroom and the activities they perform before sleep, with strategies developed by researches. Intervention with experimental group conducted with the serious game “Perfect Bedroom” will happen twice a week, for 3 weeks in a row, resulting in six sessions of 50 min each. Inferential analysis will be conducted for comparisons between groups and intragroups to measure effect of intervention in primary outcomes (sleep habits) and secondary outcomes (sleep parameters). We expect that the intervention with this game can provide valuable evidence to a new approach in promoting healthy sleep habits, with applications in clinical, educational, and familiar settings, which could diminish future health issues and risk at psychiatric diseases, decreasing the social burden of treatments for these conditions in children.

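### The unit of allocation is stated inconsistently; if arm is fixed by class, as the coin flip implies, the child-level tests and the sample size wrongly assume independent children

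*Protocol article*

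**What the plan says.** **Allocation.** Design and Procedures gives two processes. The first works on classes, by coin flip: "The first will select which classes will compose the experimental and control groups in each school". The second uses an online tool, which "will be used to allocate participants of each class with valid data for analysis to each group". The numbered list at the start of that section, and the Abstract, describe randomising the individual participants.

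**Delivery.** The game is played at school during the experimental children's classes, in sessions led by three researchers. Controls follow the normal school timetable.

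**Analysis.** Under Intergroup and Intragroups Analysis, the sleep and sleep-hygiene variables "will be compared between experimental and control groups, during the three points in time where they will be evaluated", using an independent t-test or chi-square test. The section evaluating the game names the same tests for the learning outcomes. Neither section contains a term for class or school.

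**Sample size.** The Participants section says "This study aims to recruit 176 healthy children enrolled in two private schools from Natal" and that "the number of children per class in these educational institutions ranges from 23 to 28". G*Power was run "with alpha level of 5%, effect size of 0.5, and power of 95% for the two groups", and "Results from this analysis indicated 88 participants to each group". The sidedness of the test is not stated, and there is no ICC or design effect.

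**The concern.** The independent t-test, the chi-square test and the G*Power calculation all take each child as a separate piece of evidence. If arm is decided for whole classes, children in one class share a grade, a timetable and, in the game arm, the same group sessions. Their outcomes are then likely to be correlated, and the number of independent units is nearer the number of classes than the number of children. For any positive class-level correlation the planned standard errors are too small, p-values too low and confidence intervals too narrow. With so few classes, one or two unusual ones could produce a significant result that has nothing to do with the game. The power claimed for 88 per group fails for the same reason.

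The protocol's own wording leaves it unsettled whether this is the design, because the unit of allocation is described in two ways.

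**Working it through.** **1. Reproduce the stated 88.** Inputs from Participants: effect size d = 0.5, alpha 5%, power 95%, two equal groups. With the noncentral t distribution for two independent samples:

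- one-sided 5%: smallest n = 88 per group, power at 88 = 95.1%;
- two-sided 5%: smallest n = 105 per group, power at 88 = 91.0%.

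So 88 is a one-sided calculation on independent children with no allowance for classes.

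**2. Number of classes.** 176/28 = 6.3 and 176/23 = 7.7, so full classes would number about 6 to 8, or 3 to 4 per arm. For the check, take 8 whole classes split 4 and 4: 176/8 = 22 children each, just under the documented range.

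**3. Effect on the planned test.** The documents give no ICC, so 0.01 to 0.10 is assumed. With m = 22:

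- design effect DE = 1 + (m − 1) × ICC;
- effective n per arm = 88/DE;
- two-sided type I error of the planned t-test ≈ 2 × [1 − Φ(1.96/√DE)].

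Example at ICC 0.05: DE = 1 + 21 × 0.05 = 2.05; effective n = 88/2.05 = 42.9; 1.96/√2.05 = 1.37; type I error ≈ 17.1%.

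The last column is a simulation of 20,000 trials with no true effect.

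| Assumed ICC | DE | Effective n per arm | Type I error, formula | Type I error, simulated |
|---|---|---|---|---|
| 0 | 1.00 | 88.0 | 5.0% | 5.1% |
| 0.01 | 1.21 | 72.7 | 7.5% | 7.5% |
| 0.02 | 1.42 | 62.0 | 10.0% | 9.6% |
| 0.05 | 2.05 | 42.9 | 17.1% | 17.4% |
| 0.10 | 3.10 | 28.4 | 26.6% | 27.6% |

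At the documented class sizes of 23 to 28, the formula gives slightly more: 7.6–8.2%, 10.2–11.4%, 17.6–20.1% and 27.3–30.8% for the four positive ICCs.

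**4. Power of a valid test.** A t-test on class means has 2 × 4 − 2 = 6 degrees of freedom and noncentrality 0.5 × √(effective n/2). Example at ICC 0.05: 0.5 × √(42.9/2) = 2.32.

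| Assumed ICC | Noncentrality | Power, one-sided 5% | Power, two-sided 5% |
|---|---|---|---|
| 0 | 3.32 | 90% | 79% |
| 0.01 | 3.02 | 84% | 71% |
| 0.02 | 2.78 | 79% | 64% |
| 0.05 | 2.32 | 66% | 49% |
| 0.10 | 1.88 | 51% | 36% |

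The simulation agreed to within about one percentage point, and the class-mean test held its 5% level at every ICC. The first row shows that some of the loss comes from having only 6 degrees of freedom, before any correlation enters.

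**5. Sensitivity to class numbers.** If only some children in each class take part, more classes are needed. With 8 classes of 11 per arm (no participation rate is documented, so this is only an illustration), DE = 1 + 10 × ICC runs from 1.10 to 2.00. The planned test's type I error is then about 6% to 17%, and class-level power is 91% to 72% one-sided or 84% to 59% two-sided. The problem shrinks but remains.

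**The case against.** **Children may be randomised within classes.** This is the strongest objection. The second step can be read as assigning children of each class to both arms, and the numbered list and the Abstract support individual randomisation. On that reading class effects fall on both arms and largely cancel, so the figures in step 3 do not apply. What remains is correlation from playing the game in groups, which affects the experimental arm only. This stands as a reason to make the finding conditional. It does not remove it: if each class already has an assignment, re-randomising its children makes the coin flip pointless and puts both arms in one classroom. The more coherent reading is that arm is fixed by class and the second step picks children with usable data, but that is an inference.

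**The ICC is unknown and could be small.** The main outcome is parent-reported sleep habits at home, and nothing in the document supports a value as high as 0.10. At 0.01 the type I error is about 7.5%. This is fair: the size is an assumption, and only the direction is certain for a positive ICC.

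**The power comparison must be like for like.** A reader might set two-sided power of 36% to 71% against the stated 95% and blame clustering for the whole gap. The documents do not support that. The 95% is reproduced only one-sided, so the matching range is 51% to 84%, and two-sided power is already 91% with independent children.

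**Shared parent meetings.** A reader might also infer that parents meet class by class, adding to the correlation. The text describes meetings with parents, and a workshop for the experimental group's parents, but does not say that they are organised by class.

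**A fuller analysis plan may deal with this.** That would answer an omission. Here the article itself names tests that assume independence and gives a sample size on the same basis.

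**Conclusion.** The concern holds in conditional form. The statements on allocation contradict each other and have to be reconciled. If arm is fixed by class, the stated analysis and sample size are wrong for the design: with 4 classes of 22 per arm and an assumed ICC of 0.01 to 0.10, type I error is about 7% to 27%, and valid power at an effect size of 0.5 is about 84% to 51% one-sided or 71% to 36% two-sided. These sizes rest on the assumed ICC, equal class sizes, an even split of classes and a continuous outcome. If children are randomised within classes, the inflation is much smaller and the only remaining source is group play in the game arm. An unqualified claim that the trial's error rate is inflated by these amounts would go beyond the text.

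**What to change.** 1. State the unit of allocation, say what the online tool does after the coin flip, and bring the Abstract and the numbered design steps into line.
2. If the unit is the class, replace the child-level between-group tests with a t-test on class means, or a mixed model with a random class intercept, a fixed school effect and small-sample degrees of freedom (Satterthwaite). Both can be run in SPSS, the software already named. For binary outcomes, class-level proportions are the cautious choice: a logistic mixed model on so few classes was not checked here.
3. If children are randomised within classes, say so, and consider the correlation from group play in the game arm.
4. Report the ICC. Restate the power with its sidedness and the number of classes over a plausible ICC range.

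**Cost.** The analysis change needs new wording and no new data. Confidence intervals will be wider and the stated power lower. Wording cannot restore that power. Multiplying by the design effect at the documented class sizes gives, even at ICC 0.01, 88 × 1.22 to 88 × 1.27, or 108 to 112 children per arm one-sided. From the two-sided base of 105 it gives 129 to 134. Both are before any correction for the small number of classes.
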